### Data collection and management

All outgoing and incoming text messages will be automatically recorded on the WelTel platform. The platform also captures all of the “problems” noted by participants, instances of non-response, and actions taken in relation to participants’ ‘problem’ responses and non-responses. Platform data will be backed up every 7 days.

All questionnaires will be paper-based and the data manager will then enter data into a database at the central office on an ongoing basis. A data manager will check the forms for completeness and quality will be verified by re-checking a random sample of 10 % of the data. Any problems that arise will be resolved promptly. Participant files will be stored in a locked office at the trial sites.

Data on attendance, HIV care clinical indicators like viral load and CD4 cell count as well as treatment regimen will be collected medical records. We will also collect information on demographic characteristics (age, education level, marital status and parity) of all screened patients/potential trial participants.

Qualitative research using in –depth interviews will also be performed to discover ‘how’ and ‘why’ the intervention works to improve retention in PMTCT program. Purposive sampling will be used to identify participants for qualitative interviews. Face-to-face interactions will be used to build trust during the interview process and to enhance free interaction between the researcher and the participants [20]. All conversations will be recorded with permission from the respondents and the interviews will be performed at a place and in a language preferred by the respondent.

All qualitative research tools will be developed in English, then translated to Kiswahili, and then back translated to English. The interview guide will be available in both languages.

### Analysis

#### Statistical methods

Baseline participants’ characteristics will be reported separately by treatment arm. Baseline characteristics include: age, parity (nulliparous versus previous birth), marital status (single, married or cohabiting, divorced/widowed), ARV exposure (experienced vs. naive), duration of known HIV diagnosis (newly vs. previously diagnosed), age (18–29, 30–39, 40–49, ≥50 years of age), phone ownership (owned vs. shared), level of education (none, primary, secondary, post-secondary), distance from clinic (≤1 h vs. >1 h), number of children born after HIV diagnosis, on ARV at enrolment (yes, no), time on ARV at enrolment (≤6 months, 7–12 months, ≥13 months) and HIV status disclosure (yes, no). We will report the mean (standard deviation [SD]) or median (first quartile, third quartile) for continuous variables, and count and percentages for categorical variables. All analyses are by *intention-to-treat* i.e. according to the study group to which women were originally allocated regardless of subsequent intervention received and per protocol. Other more statistical methods will be used to take into account switching.

For the primary outcome, we will compare the proportion of mothers living with HIV and their HIV-exposed infants in the program at 24 months post-birth in the intervention vs. control arm using both parametric (Chi-Square) and exact (Fisher) statistical tests. Secondary outcomes will also be compared between arms, with t-tests for normally distributed variables, Mann Whitney-U tests for non-normally distributed variables, and Chi-Square and Fisher exact tests for categorical variables. The relative risk (RR) for PMTCT retention with 95 % confidence intervals will be computed and the number needed to treat to prevent one non-retained mother-infant pair will also be estimated. Concerning the secondary outcomes, average treatment effects (ATE) will be computed for continuous outcomes and RRs for categorical outcomes. For both primary and secondary outcomes, log-linear or linear regression models will be used to provide effect estimates adjusted for potential imbalances in baseline participants’ characteristics, if required. We will repeat the analysis of primary and secondary outcomes within such subgroups (in relation to socio-demographics) to assess the homogeneity of the intervention effect across pre-determined subgroups of patients. Stratified RRs and ATEs will be computed. Regression models, which include the intervention allocation and subgroup-defining variables and their interaction, will be applied to assess effect modification across groups; all statistics tests will be run based on two side *p*-values and values <0.05 will be considered statistically significant. All statistical analyses will be again performed with Stata version 14.1 (Stata Corporation, College Station, TX, USA).

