### Sample size

The primary outcome of the study is defined as the proportion of mother-newborn retained in PMTCT care at 24 months; assuming i) a power of 80 %, ii) a two-sided test (alpha = 0.05), iii) and based on prior knowledge, a proportion retained in the control group of about 30 %, a sample size of 300 participants in each arm for a total of 600 subjects, with 5 % dropout rate (i.e. women who decide to withdraw from the study) in both the control and intervention arms was estimated to detect a 11 % difference (the smallest detectable difference) in the primary outcome between the intervention and control arms that is the difference that it would be important to detect is 11 %, computed as the proportion retained in the intervention arm minus the proportion retained in the control arm i.e. the proportion retained in the intervention group minus the proportion retained in the control group. Calculations were performed using Stata 14.1.

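### All analyses are declared both intention-to-treat and per protocol, and the primary outcome has two tests, with nothing saying which result decides the trial

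*Protocol article*

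**What the plan says.** The Statistical methods section puts all analyses under intention-to-treat, explains this as analysis by allocated group, and in the same sentence adds a second set: "regardless of subsequent intervention received and per protocol. Other more statistical methods will be used to take into account switching". Neither set is called primary or supportive. The switching methods are not named.

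The same section compares the primary outcome, retention of the mother-infant pair at 24 months after birth, "using both parametric (Chi-Square) and exact (Fisher) statistical tests". Categorical secondary outcomes get the same pair of tests. Continuous ones get a t-test or a Mann-Whitney test according to their distribution. The rule for all tests is that two-sided p-"values <0.05 will be considered statistically significant".

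The Sample size section assumes one comparison, planned as "a two-sided test (alpha = 0.05"). Its other inputs are "a proportion retained in the control group of about 30" per cent and a target difference of 11 points, which lead to "a sample size of 300 participants in each arm for a total of 600 subjects". Withdrawal of 5% is allowed for in both arms.

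**The concern.** The two sets answer different questions. Intention-to-treat ignores what the woman received, while per protocol conditions on it. Giving both the same billing for all analyses, with one significance threshold and no order between them, leaves open which p-value answers the primary objective.

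The ambiguity matters more than usual here because of what adherence could mean. Only WelTel women have a weekly message to answer. The Secondary outcomes section measures adherence to WelTel by whether a woman responds within 7 days, and it also uses non-response as its marker of ARV non-adherence when supply is thought to have run out. The primary outcome is itself staying in care. A per-protocol set built on SMS response would therefore remove women from one arm only, for behaviour close to the outcome. At stake is a claim of effectiveness, in an open trial meant to inform scale-up, that randomisation does not support.

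**Working it through.** **1. The plan's own figure.** Inputs from the Sample size section: 30% versus 41%, two-sided 0.05, 80% power.

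n per arm = [1.960·√(2·0.355·0.645) + 0.842·√(0.30·0.70 + 0.41·0.59)]² / 0.11² = (1.326 + 0.566)² / 0.0121 ≈ 296.

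This is close to the stated 300, which gives 80.5% power. After 5% dropout, 300 × 0.95 = 285 per arm, with 78.5% power. The design figure is reproduced well enough, and 285 per arm is used below.

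**2. Chi-square against Fisher.** Exact enumeration of the two binomials, 285 per arm:

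| Truth | Chi-square p<0.05 | Fisher p<0.05 | Disagree |
|---|---|---|---|
| 30% v 30% | 5.04% | 4.03% | 1.0% |
| 30% v 41% | 78.6% | 75.9% | 2.7% |

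Every Fisher rejection was also a chi-square rejection. Running both therefore adds no error beyond chi-square alone. It leaves a narrow band in which the verdict is undefined.

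**3. Per protocol with no true effect.** Let r be the share of WelTel women excluded and q their retention. The documents give neither, so both are assumptions. True retention is 30% in both arms and no control woman is excluded. Retention in the remaining WelTel women is

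p = (0.30 − r·q) / (1 − r).

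The chance of p<0.05 comes from simulation with the pooled z test. A normal approximation agrees. For r = 40% and q = 15%:

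- p = (0.30 − 0.06)/0.60 = 0.40, with 285 × 0.60 = 171 WelTel women left.
- Pooled proportion = (285·0.30 + 171·0.40)/456 = 0.3375.
- Null standard error √(0.3375·0.6625·(1/285 + 1/171)) = 0.0457; unpooled standard error √(0.21/285 + 0.24/171) = 0.0463.
- Φ[(0.10 − 1.96·0.0457)/0.0463] ≈ 0.59.

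| r | q | p | Difference | Per-protocol p<0.05 |
|---|---|---|---|---|
| 40% | 15% | 40.0% | +10.0 points | 59% |
| 30% | 16% | 36.0% | +6.0 points | about 29% |
| 20% | 18% | 33.0% | +3.0 points | 11% |
| 20% | 10% | 35.0% | +5.0 points | 23% |
| 10% | 10% | 32.2% | +2.2 points | 9% |
| 30% | 0% | 42.9% | +12.9 points | 83% |
| 20% | 30% | 30.0% | 0 | 5% |
| 10%, 20%, 30% | 40% | 28.9%, 27.5%, 25.7% | −1.1, −2.5, −4.3 points | not computed |

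The first three rows are the main scenarios. The others show how far the result moves. At the harsh end (30% excluded, none retained) the spurious difference exceeds the 11-point target. At q = 30% it vanishes, and above that it reverses.

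**4. Cost of leaving the choice open.** If success may be claimed on either intention-to-treat or per protocol (chi-square, 285 per arm, 200,000 simulated null trials), the error rate is about 6% to 7% even when exclusions are unrelated to retention (q = 30%; r = 10% to 30%). With q = 10% it is 11%, 25% and 53% for r = 10%, 20% and 30%. With intention-to-treat and chi-square alone it is 5.0%.

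**The case against.** The strongest reply is that the per-protocol set is not defined. Exclusion by SMS engagement is an inference from how the protocol measures adherence elsewhere. The mention of switching suggests movement between arms, and departures from the eligibility criteria could arise in either arm. The definition and the switching methods may sit in an analysis plan that is not shown, and their absence is not the point made here. This stands. A reader might infer that the per-protocol analysis is biased towards WelTel as a matter of fact; the documents do not support that. The Intervention section also sends non-responders to a nurse and to tracing by telephone and then at home, so their retention need not be poor.

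Second, intention-to-treat comes first and is the only set explained, and nothing says that a per-protocol result alone would establish success. Reporting both is common practice. This is fair as a guess at intent, but the sentence assigns all analyses to both sets, and no other text ranks them.

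Third, the double testing does little harm. This also stands. A reader might infer that two tests inflate the error rate, or that every analysis is tested twice. The enumeration rules out the first for the primary comparison, and the continuous secondary outcomes contradict the second.

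**Conclusion.** The concern holds in a limited form. The protocol itself gives intention-to-treat and per protocol equal rank and does not say which of two tests is decisive for the primary outcome. The ranking of analysis sets is the part that matters. Without a hierarchy, the error rate exceeds 5% modestly when exclusions are unrelated to retention, and substantially when they are selective.

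The 11% to 59% range for a significant per-protocol result under no effect rests on four assumptions: 30% true retention in both arms, 285 per arm, exclusions in the WelTel arm only, and excluded women retained at 15% to 18%. Favouring WelTel is the likely direction if exclusion follows SMS engagement, but it is not certain. The chi-square/Fisher question is a minor matter of wording.

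**What to change.** State in the Statistical methods section that the primary conclusion rests on one analysis: intention-to-treat in all randomised women, with a CMH test stratified by clinic, two-sided at 0.05. Stratification fits the design because the Randomization and allocation section randomises separately at each clinic. Label the per-protocol analysis, any switching analysis and the Fisher test as supportive only.

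Do not replace per protocol with a complier-average effect based on an SMS-engagement threshold. That estimate needs the intervention to have no effect on women below the threshold. Under the Intervention section, non-response itself triggers nurse contact and tracing, so these women still receive an active part of the intervention, and any benefit to them would be credited to the engaged women.

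The cost is a few sentences, with no change to data collection or sample size. The downside is that a positive per-protocol result can no longer support a claim on its own.

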### Randomization and allocation

Eligible and consenting patients will be randomized to the intervention and control arms using a 1:1 allocation ratio. To ensure balance between the arms throughout the trial, we adopted a permuted-block randomization scheme. The block size will be concealed until the trial is over. Randomization will be performed separately at each clinic. We will use opaque sealed envelopes to assign participants to the intervention and control arms. The randomization list was be generated at the Karolinska Institutet (Stockholm, Sweden) by an independent statistician.

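### Randomisation is stratified by clinic but the primary test ignores clinic and adjustment is conditional: the test stays valid, but power is forgone if retention differs between clinics

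*Protocol article*

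**What the plan says.** All references are to the protocol article.

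- **Randomization and allocation:** 1:1 permuted blocks, and "Randomization will be performed separately at each clinic". Clinic is therefore a stratification factor.
- **Study setting:** 4–7 facilities in western Kenya, chosen as a mix of urban and rural sites, all within one HIV care programme.
- **Statistical methods, primary outcome:** the arms are compared "using both parametric (Chi-Square) and exact (Fisher) statistical tests". A relative risk (RR) with 95% confidence interval follows. Clinic enters neither, and the text does not say which of the two tests decides.
- **Statistical methods, adjustment:** "log-linear or linear regression models will be used to provide effect estimates adjusted for potential imbalances in baseline" participant characteristics, but only where needed. No criterion for need and no covariate set is given.
- **Statistical methods, baseline list and subgroups:** the list includes travel time to the clinic but not the clinic itself. The stratified RRs concern socio-demographic subgroups, not clinic.
- **Sample size:** "assuming i) a power of 80" %, "a two-sided test (alpha = 0.05"), "a proportion retained in the control group of about 30" %, and "a sample size of 300 participants in each arm for a total of 600 subjects", which with 5% dropout "was estimated to detect a 11 % difference".

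**The concern.** Balancing the arms within each clinic takes between-clinic variation out of the treatment contrast. An unstratified 2×2 test still counts that variation in its standard error. If retention differs by clinic, the standard error is too large: the test rejects less often than 5% under the null, the interval is too wide, and a true effect is harder to show than it need be. The sites were chosen to differ in setting, so some difference in retention is plausible.

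The adjustment clause raises a second, smaller matter. Covariates enter according to the imbalance that happens to be seen. The adjusted RR then depends on the data, and the reader cannot tell in advance which estimate leads.

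Neither matter is a detail left to an analysis plan. The article itself fixes the test and the adjustment rule.

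**Working it through.** **1. The plan's own figure.** With p0 = 0.30, p1 = 0.41 and mean 0.355:

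n = [1.96·√(2·0.355·0.645) + 0.842·√(0.30·0.70 + 0.41·0.59)]² / 0.11² = (1.326 + 0.566)² / 0.0121 ≈ 296 per arm.

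The stated 300 is reproduced before dropout. Full inflation would give 296/0.95 ≈ 312. Power is 80.5% at 300 per arm and 78.5% at 285 (300 × 0.95). The small shortfall at 285 comes from dropout, not from clinic.

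**2. Why the unstratified test is conservative.** Under the null, with equal clinics and arms balanced within clinic, the variance of the risk difference is (2/n)·mean[p_k(1−p_k)]. The unstratified test uses (2/n)·p̄(1−p̄). The ratio of true to assumed variance is

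r = 1 − Var(p_k) / [p̄(1−p̄)], with p̄(1−p̄) = 0.30·0.70 = 0.21.

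The effective critical value is 1.96/√r, so the true size is 2·[1 − Φ(1.96/√r)]. The standard error is too large by the factor 1/√r.

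**3. Numbers.** The spread of control retention between clinics is an assumption, because the article gives none. Five evenly spaced clinics are used, with 57 per arm in each (5 × 57 = 285). Power is simulated (200,000 trials per row) with a common odds ratio set to give a mean of 41%.

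| Control retention by clinic | Var(p_k) | r | Size, formula | SE too large by | Power, chi-square | Power, CMH | Gain (points) |
|---|---|---|---|---|---|---|---|
| all 30% | 0 | 1 | 5.0% | 0% | 78.6% | 78.6% | 0 |
| 20–40% | 0.0050 | 0.976 | 4.7% | 1.2% | 78.9% | 79.5% | 0.6 |
| 15–45% | 0.01125 | 0.946 | 4.4% | 2.8% | 79.4% | 81.1% | 1.8 |
| 10–50% | 0.0200 | 0.905 | 3.9% | 5.1% | 79.7% | 82.7% | 3.0 |

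A separate run of 40,000 trials gave unstratified sizes of 5.1%, 4.7%, 4.3% and 4.0% and gains of 0, 0.8, 1.8 and 3.1 points. CMH size stayed near 5% throughout.

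**4. Number of clinics.** With a constant 11-point difference in every clinic, the gain for 4 / 7 clinics is 0.6 / 0.5 points at 20–40%, 1.7 / 1.3 at 15–45% and 2.8 / 2.3 at 10–50%.

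**5. Fisher's test.** With identical clinics its size is about 4% and it loses about 2.6 points against CMH. That part is discreteness, not clinic. At 10–50% the total loss is 5.5 / 5.1 points for 4 / 7 clinics.

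**6. Conditional adjustment.** Assume 12 independent binary covariates, five of them prognostic, with adjustment triggered by imbalance at p < 0.05. At least one trigger is expected by chance in 1 − 0.95¹² = 46% of trials; simulation of 5,000 trials gave about 45%. Size was 0.054 unadjusted, 0.051 with imbalance-selected adjustment, and 0.057 if the more favourable of the two is taken. Power was 78.1% unadjusted, 77.9% with imbalance-selected adjustment, and 78.6% with all covariates fixed in advance.

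**The case against.** The best defence is that the planned test is valid. Leaving out a stratification factor errs on the safe side, and every size above is at or below 5% within simulation error. This stands: a reader might infer a threat to type I error, and there is none.

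A reader might also infer that ignoring clinic pulls the trial below its design power. It does not. Chi-square power stays at 78.6–79.7% across the table, at or slightly above the 78.5% that the design gives at 285 per arm. What is missed is an additional gain.

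The size of that gain rests on a spread the article does not supply. All facilities belong to one programme using the same PMTCT option, so an urban and rural mix alone does not establish very wide differences. Gains well above 3 points need more extreme spreads, for which the article offers no support.

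The conditional clause could be read as a serious source of bias. The article plans an RR before it mentions adjustment, so the adjusted model may be only supplementary, and the simulated harm is small. What remains is that the text does not say which estimate leads, in an open-label trial where that choice is best made beforehand.

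Finally, nothing in the article shows which baseline factors predict retention here. Only the inclusion of clinic follows from the design.

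**Conclusion.** The point holds as a matter of efficiency and pre-specification, not validity. The primary test does not match the randomisation. The cost is nil if clinics retain equally well, under 1 point of power at 20–40%, about 1.8 at 15–45% and about 3 at 10–50%, with true size falling from about 5% to about 4% and standard errors up to 5% too large. These figures assume 285 evaluable per arm, 30% v 41%, and five equal clinics with evenly spaced control rates. The direction does not depend on the spacing; the size does. The data-dependent adjustment adds ambiguity about the leading estimate but little measurable error. The change is worth making because it costs almost nothing and the sample size leaves a thin margin: at 15–45%, CMH reaches the stated 80% power and chi-square falls just short.

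**What to change.** - Name one primary analysis, stratified by clinic: a CMH test with Mantel-Haenszel RR and risk difference, or a log-binomial or modified Poisson model with clinic as a fixed effect. This also settles which of the two listed tests decides.
- Include clinic in the secondary-outcome models.
- Replace conditional adjustment with a short covariate list, fixed in advance from baseline data already collected and used whatever imbalance is seen. The choice of covariates is the sponsor's. State whether the adjusted or the unadjusted estimate leads.

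The cost is analysis wording only. Clinic is known for every participant from the randomisation, the required sample size does not rise, and CMH loses essentially nothing if clinics turn out alike.

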#### Secondary outcomes

Adherence to the WelTel SMS intervention measured as the proportion of women living with HIV who do not respond to the SMS within 7 days.Adherence to (i) ARVs measured as the proportion of women living with HIV who do not respond to the SMS within 7 days when suspected to be out of ARVs (i.e. failure to pick up ARVs that can cover her absence); (ii) facility-based delivery measured as the proportion of women who deliver in hospital; (iii) early infant HIV testing defined as the proportion of HIV-exposed infants who are tested for HIV within 8 weeks of birth measured as HIV –exposed infants with known HIV status at age 10weeks and (iii) exclusive breastfeeding defines as feeding the HIV-exposed infant only milk from the mother’s breast.Participant perceived facilitators and barriers of the WelTel SMS intervention (assessed as perceived reasons and challenges of use as well as suggestions to possible solutions).Cost compared with (i) effectiveness (levels of retention) from a payers’ perspective and (ii) quality of life (differences in pregnant women’s QALYs between the two trial arms.

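### Subgroup homogeneity is to be assessed partly by repeating significance tests stratum by stratum at p<0.05, and the plan does not say that subgroup claims rest on the planned interaction tests

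*Protocol article*

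**What the plan says.** The relevant text is in the protocol article, Analysis, Statistical methods. After setting out the overall comparisons (chi-square and Fisher tests for categorical outcomes, t or Mann-Whitney tests for the others), it continues: "We will repeat the analysis of primary and secondary outcomes within such subgroups". The subgroups are described only as "in relation to socio-demographics". The stated purpose is "to assess the homogeneity of the intervention effect across pre-determined subgroups of patients". Stratum-specific relative risks (RRs) and average treatment effects (ATEs) will be given.

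The section then adds a second approach, "Regression models, which include the intervention allocation and subgroup-defining variables and their interaction", to assess effect modification. It closes with one rule for all tests, two-sided, under which "values <0.05 will be considered statistically significant".

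The article does not name the subgroup variables. The nearest candidates are the baseline characteristics in the same section, for example "marital status (single, married or cohabiting, divorced/widowed" and "level of education (none, primary, secondary, post-secondary", and the four demographic items under Data collection and management (age, education level, marital status, parity). The Sample size section powers only the overall primary comparison.

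**The concern.** Repeating the analysis within subgroups, read with the rule for all tests, yields a p-value for each outcome in each stratum, and any below 0.05 is called significant. That is a poor method for the purpose the section itself gives. Homogeneity concerns the difference between stratum effects, and only the interaction test addresses it. Comparing which strata reach significance mainly reflects stratum size and chance.

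Both methods are planned, they share one threshold, and nothing says which one decides. A report could therefore follow this plan and still state that the intervention works in one group of women and not in another on stratum p-values alone. The Discussion part of the Abstract says that results will inform policy and potential scale-up, so such a statement could affect who is offered the service.

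**Working it through.** **1. The plan's own sample size.** Inputs from Sample size: control retention 30%, difference 11 points (so 41%), two-sided alpha 0.05, power 80%, 300 per arm, 5% dropout. The usual two-proportion formula gives 296 per arm before dropout, which agrees with 300. With 300 × 0.95 = 285 evaluable per arm, power is 78.5%. The overall comparison is thus powered about as stated, with no reserve for subgroups.

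**2. A uniform effect, tested half by half.** Assumption: a two-level factor splits the sample evenly and the true effect is 30% versus 41% in both halves. Evaluable per arm in each half: 285/2, about 142.
- Pooled proportion: (0.30 + 0.41)/2 = 0.355.
- SE under the null: √(2 × 0.355 × 0.645/142) = 0.0568.
- SE under the alternative: √((0.41 × 0.59 + 0.30 × 0.70)/142) = 0.0564.
- Power: Φ((0.11 − 1.96 × 0.0568)/0.0564) = Φ(−0.023) = 0.49.
- Exactly one half significant: 2 × 0.49 × 0.51 = 0.50.
- Both significant: 0.49² = 0.24. Neither: 0.51² = 0.26.

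So for one balanced factor, on the primary outcome, an effect that is the same for everyone appears to be present in one group and absent in the other half of the time.

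**3. How many tests.** The article gives no counts, so these are assumptions.
- Outcomes comparable between arms: 4 to 6. Four are retention, hospital delivery ("facility-based delivery measured as the proportion of women who deliver in hospital"), early infant testing and exclusive breastfeeding. Up to two quality-of-life measures may be added. The two outcomes defined by SMS response are left out, because only the intervention arm is texted.
- Factors: 4 (age, parity, marital status, education) to 6 (adding phone ownership and distance). With age in three bands, since few pregnant women will be 50 or older, the strata number 3 + 2 + 3 + 4 = 12, or 16 with the two further two-level factors.

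**4. Chance of at least one false positive.** If tests are independent, the chance is 1 − 0.95^m.
- Within strata, 12 × 4 = 48 tests: 1 − 0.95^48 = 0.915.
- Interactions, 4 × 4 = 16 tests: 1 − 0.95^16 = 0.56, with 0.8 expected.
- Interactions, 6 × 6 = 36 tests: 1 − 0.95^36 = 0.84, with 1.8 expected.
- Interactions, primary outcome only: 1 − 0.95^4 = 0.19 and 1 − 0.95^6 = 0.26.

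The tests are not independent, so this was also simulated: 600 women, 1:1, no effect on any outcome, binary outcomes at 30%, latent correlation between outcomes 0 to 0.6, assumed stratum shares, 1,500 trials per setting, with a heterogeneity test across strata standing in for the regression interaction.

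| Setting | Any false within-stratum result | Any false interaction |
|---|---|---|
| 12 strata, 4 outcomes | 0.83–0.87 | 0.52–0.57 |
| 16 strata, 6 outcomes | 0.95–0.98 | 0.78–0.84 |
| Primary only, 12 strata | 0.38 | 0.19 |
| Primary only, 16 strata | 0.46 | 0.28 |

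The two columns need different conditions. The within-stratum figures require that the intervention does nothing for any outcome in any stratum. The interaction figures require only that there is no heterogeneity; with a non-zero uniform effect, they hold on the scale on which the effect is uniform.

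**The case against.** The same section supplies much of what good practice asks for. It states a homogeneity purpose, calls the subgroups pre-determined, gives stratum-specific estimates and plans treatment-by-subgroup interaction models. The 0.05 sentence can be read as a general convention. The article is a condensed document, and the list of subgroups and any multiplicity handling may sit in an analysis plan that is not shown. All of this stands, and neither the missing subgroup list nor the absence of a multiplicity adjustment is held against the plan here. What remains is that the text also commits to repeating the tests within strata, applies the significance label to all of them, and does not say that the interaction test decides.

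A reader might infer three stronger things that the document does not support.
- *False subgroup claims are almost certain.* The counts behind such a figure are not in the article. The probability comes close to 1 only for within-stratum tests pooled over many outcomes and strata, with no effect anywhere. For interactions on the primary outcome it is 19% to 28%.
- *Significant subgroup results would mostly be false.* If the intervention works, a significant stratum can be a true positive. The error is then in reading a non-significant stratum as lack of effect, which is what step 2 of the working measures.
- *The plan does not set the primary comparison apart.* It does: objectives and outcomes are divided into primary and secondary, and the sample size rests on the one primary outcome.

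**Conclusion.** The point holds in a limited form. The plan uses within-stratum significance as one means of assessing homogeneity, which it cannot do, and it leaves open whether subgroup claims will rest on the interaction tests. The firmest figure is the 50% chance that a uniform effect looks significant in exactly one half. It uses the protocol's own rates and sample size, plus the assumption of one evenly split factor. The multiplicity figures show the order of magnitude only, since they depend on assumed numbers of factors, strata and outcomes and on assumed stratum shares. The overall primary test and its 5% error are unaffected. This is a cheap improvement and does not threaten the trial's main conclusion.

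**What to change.** State in the analysis plan that effect modification will be judged only by the interaction tests already planned. Report stratum-specific RRs and ATEs with 95% confidence intervals, without within-stratum p-values or significance statements. Label subgroup results exploratory, and limit the 0.05 sentence so that it does not cover tests within strata. Subgroup analysis of the secondary outcomes can stay, and the secondary outcomes need no relabelling for this purpose.

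The change is to wording only: no new data, no change in sample size and no new models. The cost is fewer nominally significant subgroup statements in the report.
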